### Tertiary outcome measure

The care-related strain to support partners is measured with the Caregiver Strain Index (CSI). The CSI is a caregiver-specific measure that asks whether aspects of the caregivers’ lives, such as sleep, finances and normal routine have been affected by their caring role, and whether this has placed a physical and mental strain upon them [23, 24]. The CSI includes thirteen items that are scored with Yes (1) or No (0) yielding a total score between 0 and 13. A higher score indicates higher care-related strain, and caregivers' self-reports of experiencing situations that conflict with giving help are associated with CSI scores of 7 or higher [21].

### Other baseline data

Disability is measured by use of the EDSS.The EDSS is based on a neurological examination that provides the basis for the assessment of several functional systems that, according to predefined algorithms, contribute to the EDSS score [25].

### Statistical aspects

Based on the differences in MSSES control scores between baseline and at 6 months after CDT found in RRMS patients with EDSS score <4.0 in the explorative observational study [12], we conducted the following power analysis. We assume at 6 months an average of 650 for the experimental group and an average of 560 for the control group (an increase of 10 points compared to the baseline average found in the observational study). Assuming an SD of 200 on the 6 months measurement we would need 79 patients per group in order to obtain a power of 80 %, when using a two-sided t-test with an alpha of 5 %. However as we will use the baseline measurement in the analysis this number has to be multiplied by a design factor equalling 1 – r^2^_baseline, 6 months_. Assuming a correlation of 0.5 (also based on the observational data) this design factor equals 0.75. Therefore, the number of analyzable patients needed to obtain a power of 80 % equals approximately 60 per condition. Taking account of an expected drop-out of 15 %, we will include a total of 140 patients; approximately 60 with support partner and 80 without support partner.

The randomisation is performed by a statistician who is not otherwise associated with the study ([name] PhD, Signidat, Groningen, The Netherlands) via a stratified block randomisation with disease duration and gender as blocking factors. The randomisation list was made at the Department for Health Evidence (RD), Radboud university medical center, Nijmegen, The Netherlands.

The primary outcome variable is the MSSES control score after 6 months. This will be analysed using an ANCOVA with the assessment of 6 months as dependent variable and condition and baseline assessment as independent variables For all other variables the 6 months values will be analysed in a similar way. All analyses will be performed according to the intention-to-treat principle. The statistical analyses will be performed at the Department for Health Evidence, Radboud university medical center, Nijmegen, The Netherlands.

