In an explorative observational study we assessed in MS patients the effect of an intense, multidisciplinary, 3-day, social cognitive wellness program (Can Do Treatment [CDT]) with the participation of support partners [12]. It was found that in the RRMS group 6 months after the intervention the self-efficacy control had significantly increased by 25.8 %, the mental HRQoL by 22.3 % and the physical HRQoL by 17.6 %. Moreover, in the low disability (Expanded Disability Status Scale [EDSS] score <4.0) group the increase in self-efficacy control at 6 months was 23.8 % and the mental HRQoL 19.3 %.

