### Aims and objectives

The overall aim of the study is to evaluate in a randomized controlled trial the clinical and cost effectiveness of CDT, with or without the participation of support partners, in comparison to no such treatment for people with RRMS and low disability.

The primary objective is to evaluate the effectiveness of CDT compared to no such treatment in increasing self-efficacy control (primary outcome) during 6 months after treatment.

The secondary objectives are to evaluate:the effectiveness of CDT compared to no such treatment in increasing self-efficacy function, autonomy and participation, HRQoL and coping during 6 months after treatment;the effectiveness of CDT compared to no such treatment in decreasing anxiety and depression during 6 months after treatment;the cost effectiveness and cost utility of CDT during 6 months after treatment;

The tertiary objective is to evaluate the effectiveness of CDT compared to no such treatment in decreasing care-related strain in support partners during 6 months after treatment.

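### Support-partner status is a planned composition factor of the trial but is absent from the primary ANCOVA and the stratification, and the 80% power rests on an unstated average of 90 points across the partner mix

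*Protocol article*

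**What the plan says.** All references are to the protocol article.

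- **Aim (Aims and objectives).** CDT is to be evaluated "with or without the participation of support partners, in comparison to no such treatment". The primary objective that follows compares CDT with no CDT on self-efficacy control and does not mention partners.
- **Composition (Statistical aspects).** The 140 patients are "approximately 60 with support partner and 80 without support partner". Study design and organization gives the same ratio, about 3:4.
- **Source of the effect (Statistical aspects, Background).** The power calculation draws on the exploratory observational study, which Background describes as a "social cognitive wellness program (Can Do Treatment [CDT]) with the participation of support partners". The Concept section lists inclusion of the support partner among the principles on which CDT is based.
- **Planned effect (Statistical aspects).** The plan assumes "an average of 650 for the experimental group and an average of 560 for the control group". The control value is "an increase of 10 points compared to the baseline average found in the observational study".
- **Randomisation and model (Statistical aspects).** Allocation uses "stratified block randomisation with disease duration and gender as blocking factors". The primary ANCOVA contains condition and the baseline score only.

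**The concern.** The trial deliberately mixes two forms of delivery and fixes their proportions. By the article's own account one of them, attendance with a partner, is part of the concept of the intervention. The effect assumption comes from a programme described as having partners take part, yet 80/140 = 57% of the trial patients are to be without one. About half of those 80, some 40, would be in the CDT arm. The article gives no reason why 90 points should be the average for this mix.

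Two things are at stake. First, the power statement carries a condition that a reader cannot see. Second, a factor that is fixed in the design, and that must be known in both arms for the caregiver-strain outcome, is left out of the primary model. A chance difference in partner share between arms is then not adjusted for. A positive pooled result could also be read as evidence that CDT works for patients who come alone. The Discussion announces a stratified secondary analysis for on-study relapses, which the authors do not expect to matter, but none for partner status.

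**Working it through.** **1. The plan's own figures.** Inputs from Statistical aspects: difference 650 − 560 = 90, SD 200, "two-sided t-test with an alpha of 5" per cent, power 80%, baseline correlation 0.5, drop-out 15%.

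- Noncentral t: power is 0.797 at 78 per group and 0.803 at 79. This confirms "we would need 79 patients per group in order to obtain a power of 80" per cent.
- Baseline adjustment: 79 × (1 − 0.5²) = 79 × 0.75 = 59.25, about 60 per arm.
- Drop-out: 120/0.85 = 141.2, so 142; the plan has 140. Then 140 × 0.85 = 119 analysable, 59.5 per arm.
- Residual SD = 200 × √0.75 = 173.2. Power for 90 points at 59.5 per arm is 0.80.

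The stated sample size is correct for its inputs.

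**2. What the 80% depends on.** Let A be the effect with a partner and f the effect without one as a fraction of A. The average over the mix is A × (60 + 80f)/140. The documents give no value for f, so the values below are assumptions.

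With A = 90:

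| f | Average effect | Power |
|---|---|---|
| 1.00 | 90.0 | 80% |
| 0.75 | 77.1 | 67% |
| 0.50 | 64.3 | 52% |
| 0.25 | 51.4 | 36% |

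**3. A different anchor from the documents.** The control mean of 560 is 10 above the pilot baseline, so that baseline is about 550. The planned rise under CDT is 650 − 550 = 100 points, or 100/550 = 18%. Background reports a 23.8% pilot gain in the low-disability group. Applied to 550 this is 0.238 × 550 = 131 points, or 131 − 10 = 121 net of the assumed control rise.

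With A = 121:

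| f | Average effect | Power |
|---|---|---|
| 0.75 | 103.7 | 90% |
| 0.50 | 86.4 | 77% |
| 0.25 | 69.1 | 58% |

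The mix averages 90 when 121 × (60 + 80f)/140 = 90. That gives 60 + 80f = 104.1 and f = 0.55.

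This anchor is itself an assumption. The 23.8% is for the low-disability group; the gain in RRMS patients with low disability, the group used in the power calculation, is not given.

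**4. Chance imbalance.** With 70 per arm and partner share 60/140, the SD of the between-arm difference in share is √[(60/140)(80/140)(2/70)] = 0.084, about 8 percentage points.

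**5. Precision by partner status.** Analysable per arm: 60 × 0.85/2 = 25.5 with a partner, 80 × 0.85/2 = 34 without.

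- With a partner: SE = 173.2 × √(2/25.5) = 48.5; 95% half-width 1.96 × 48.5 = 95 points.
- Without: SE = 173.2 × √(2/34) = 42.0; half-width 82 points.
- Difference between the two: SE = √(48.5² + 42.0²) = 64.2; half-width 126 points, larger than the whole planned effect.

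**The case against.** A reader might infer that the power is really below 80%, because the effect was borrowed from a programme with partners and applied to patients without them. The documents do not support that. They do not say that every pilot patient brought a partner, or what share did. They nowhere say that the effect is smaller without one: the Components section calls the small group sessions the actual training and describes no component as needing a partner. The planned gain of 18% is also below the pilot's 23.8%, so some allowance may already be built in, although the article does not link it to partners. This objection stands. The first table is a sensitivity display, not a finding of low power.

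A reader might also infer that the aim of evaluating CDT in a mixed population is unsupported. It is not. The natural reading is a pooled comparison with no CDT, and 1:1 randomisation with a baseline-adjusted ANCOVA estimates that without bias. No objective compares the two modes or asks about patients without a partner alone. Omitting the covariate affects precision and chance balance only, and no passage shows that partner status is prognostic once baseline is adjusted for.

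Finally, subgroup estimates may be in an analysis plan that is not shown, and here they would be imprecise. That is fair, but the primary model and stratification factors are stated in the article, so their content can be commented on. The imprecision is a reason to label partner-specific results descriptive and to limit what the pooled result is said to show.

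**Conclusion.** The point holds in a limited form. Partner status is a planned design factor with a 60/80 split, tied to the concept of the intervention, and it is missing from the stated primary model and the stratification. The consequences are modest: unadjusted chance imbalance of about 8 percentage points (SD), and a pooled result that could be over-read.

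The power calculation is arithmetically right but conditional on an average of 90 points across the mix. How demanding that condition is depends on figures the documents do not give. If the effect with a partner is 90, patients without one must gain the same. If it is about 121, as the pilot percentage suggests under the assumptions in step 3, about 55% as much is enough. Neither bias in the primary comparison nor a shortfall in power is shown.

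**What to change.** 1. Record partner status before allocation in both arms and add it as a covariate to the primary ANCOVA.
2. Report the treatment effect by partner status, and the difference between the two, with confidence intervals labelled descriptive. Give the expected half-widths in advance: about ±95 with a partner, ±82 without, ±126 for the difference.
3. State that the primary result is the pooled effect for a mix of roughly 3:4, and that it does not by itself show that CDT works without a partner.
4. State that 80% power assumes an average of 90 points across the mix.
5. Optionally, add partner status as a stratification factor for patients still to be randomised. The article says recruitment is ongoing, but the list has been made and a further factor would thin the strata.

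The cost is one model degree of freedom, subgroup estimates that will be imprecise, and a few sentences of wording. The sample size need not change.

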## Background

Multiple sclerosis (MS) is a chronic disease of the central nervous system pathologically characterized by immune-mediated inflammation, demyelination and axonal degeneration. In most people with MS the first symptoms occur between 20 and 45 years of age, and the initial course is characterized by relapses that are followed by complete or incomplete recovery: relapsing-remitting MS (RRMS) [1]. The nature and intensity of symptoms and disabilities are variable and largely unpredictable. MS cannot be cured and despite the use of disease modifying drugs most persons with RRMS progress to the secondary progressive phase (SPMS), for which no treatment is available. Moreover, the response to disease modifying treatment in RRMS varies between persons and is difficult to predict.

Self-efficacy is a psychological concept that refers to the degree in which a person is confident to complete tasks and reach goals in specific situations [2]. It is a core component in social cognitive theory, according to which psychosocial functioning is determined by reciprocal interactions between personal factors, behavior and the environment [3, 4]. In persons with MS disabilities negatively affect independence, and the negative experience of decreasing independence may result in a decrease in self-efficacy. Low self-efficacy is associated with lower health-related quality of life (HRQoL) [5, 6], less psychological adjustment [7], impaired cognition [8, 9] and less physical activity [6]. Moreover, a lowered self-efficacy may cause patients to underestimate their actual potential, as a result of which capabilities that are still present may eventually disappear. Support partners have also to deal with patients’ disabilities and loss of self-efficacy. A more intensive appeal to them often results in an increased mental and physical strain and may eventually weigh on the relation.

A wellness program is a structured intervention focused on achieving wellness in the physical, psychological and spiritual realm [10]. In the U.S.A. the Can Do Program is a concentrated 4-day interdisciplinary educational wellness program for MS patients, that promotes health seeking behaviors, lifestyle empowerment and exercise [11]. The program aims to enable patients the uncovering of existing capabilities [11], and an improvement in self-efficacy and perceived health has indeed been observed in patients who took part in this program [11].

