### Recruitment and inclusion

Participants are recruited by the National MS Foundation The Netherlands via publications in their quarterly journal *Nieuwslijn*, postings on the website www.nationaalmsfonds.nl, information on the website of the organisation’s National MS Network (a portal for MS caregivers), information on social media (facebook, twitter, hyves), and presentations during meetings of neurologists, MS nurses and other caregivers. Persons who are interested are requested to contact the National MS Foundation The Netherlands by phone ([name]) in order to be informed about the various aspects of the CDT and of the study, like objectives and design. If they wish to receive further information, the patient information leaflet and consent form are sent to them by regular mail, and a second phone call is scheduled with an interval of at least one week. During the second contact by phone, the study assistant (AH) checks the eligibility criteria. If the patient meets the criteria, eventual questions are answered. Persons are explicitly informed that participants in the control group have the right to receive the CDT after their study participation has ended. Questions regarding the content of the CDT treatment are answered by phone by the MS nurse (MH) of the study team or by the principal investigator (PJJ). After another reflection period of at least one week, the MS nurse (MH) contacts the person and if he/she is willing to participate the inclusion procedure follows, during which by use of predefined questions the disease course (RRMS) is verified and the disability (EDSS 4.0 or less) is assessed (see below).

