## Discussion

In an exploratory observational study we assessed in people with MS the potential effectiveness and feasibility of an intensive social-cognitive program with the participation of support partners and found that in the RRMS subgroup self-efficacy control, mental HRQoL and physical HRQoL had increased by 24.8 %, 22.3 % and 17.6 %, respectively. Likewise, in persons with low disability (EDSS score 4.0 or less) the self-efficacy control and mental HRQoL had increased with 23.8 % and 19.3 %, respectively. No such changes were seen in the progressive subgroup or in persons with higher disability (EDSS > 4.0). Therefore, we conceived a randomized controlled trial to further evaluate the (cost)effectiveness of CDT in people with RRMS and low disability. Several other observational studies showed beneficial effects of various types of social-cognitive wellness programs in MS [11, 27, 28], but as yet there are no reports of randomized controlled trials [29].

We considered the MSSES control score the main outcome measure, and not the MSSES function or total score, because the pilot study showed an evident difference between the change in the self-efficacy control vs. the absence of change in self-efficacy function (+1.2 %) [12]. Conceptually, the control and functional subscales of the MSSES measure different dimensions of self-efficacy: the control subscale measures confidence with managing symptoms and coping with the demands of illness, whereas the function subscale measures confidence with functional abilities.

Having had a relapse in the preceding 4 weeks is an exclusion criterion, since we considered that being in a suboptimal condition due to clinical disease activity would increase the risk of unwanted side effects, and would also interfere with the efficacy of CDT. Participants with a relapse during the study period are not excluded from the study, as we do not expect that having experienced a relapse in the 6 month study period or experiencing a relapse at the month 6 assessment does substantially affect self-efficacy; self-efficacy is considered a rather stable trait that requires an intense intervention like CDT to be modified. To address this point in the analysis phase, we assess the on-study occurrence of relapses and will perform a stratified secondary analysis to assess an eventual effect of relapses on the primary outcome.

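### The primary ANCOVA is valid and reaches its planned power, but prespecifying baseline EDSS, already measured in every patient, could add a little precision for one degree of freedom

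*Protocol article*

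**What the plan says.** Statistical aspects names the 6-month MSSES control score as the primary outcome, to be analysed by an "ANCOVA with the assessment of 6 months as dependent variable and condition and baseline assessment as independent variables". The other outcomes are to be handled similarly. The same section stratifies the randomisation on disease duration and gender, so EDSS is not an allocation factor.

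EDSS is available for every patient. Under Recruitment and inclusion, the inclusion procedure is where "the disability (EDSS 4.0 or less) is assessed (see below"). Under Other baseline data, "Disability is measured by use of the EDSS", and it is the only measure listed there. It serves as an entry criterion, so treatment cannot influence it.

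Two passages connect disability with self-efficacy. The Background reasons that "In persons with MS disabilities negatively affect independence, and the negative experience of decreasing independence may result in a decrease in self-efficacy". The Discussion reports, for the uncontrolled pilot, that self-efficacy control rose by 23.8% in patients with low disability, and that "No such changes were seen in the progressive subgroup or in persons with higher disability (EDSS > 4.0").

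**The concern.** A baseline covariate improves an ANCOVA when it explains variation in the outcome beyond what the model already contains. The protocol relies on this principle when it shrinks the sample size by 1 − r² for the baseline score. EDSS is a natural second candidate: it costs no extra data collection, and the protocol's rationale gives a reason to expect some relation to self-efficacy.

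If EDSS does predict the 6-month score given the baseline score, omitting it has two consequences. The variation it explains stays in the error term and widens the confidence interval. A chance difference in disability between the arms also carries through to the estimate, because neither the stratification nor the model addresses it directly. The design has almost no power to spare, so even a small gain is worth having if it is nearly free.

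**Working it through.** **Inputs from Statistical aspects.** "We assume at 6 months an average of 650 for the experimental group" and "an average of 560 for the control group", so the difference is 650 − 560 = 90. "Assuming an SD of 200 on the 6 months measurement". Baseline to 6-month correlation 0.5, two-sided alpha 5%, power 80%, drop-out 15%, total 140.

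**Input not given.** The partial correlation p of EDSS with the 6-month MSSES control score, given baseline MSSES control. I assume 0 to 0.3.

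**Step 1: reproduce the plan's size.** The noncentral t-test with difference 90 and SD 200 gives power 0.7975 at 78 per group and 0.8026 at 79, so 79 is right. The ANCOVA factor is 1 − 0.5² = 0.75, and 79 × 0.75 = 59.25, or about 60 per arm. With drop-out, 2 × 59.25 / 0.85 = 139.4, or about 140. The expected analysable number is 140 × 0.85 = 119, or 59.5 per arm.

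**Step 2: power of the stated model.** Residual SD = 200 × √0.75 = 173.2. SE = 173.2 × √(2/59.5) = 31.76. Noncentrality = 90 / 31.76 = 2.834. With 116 degrees of freedom, power is 0.803. The plan delivers what it promises.

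**Step 3: add EDSS.** Residual SD becomes 173.2 × √(1 − p²), with 115 degrees of freedom. The n per arm needed is roughly 59.25 × (1 − p²).

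| Assumed p | Residual SD | Reduction in SE | n per arm needed | Power at 59.5 per arm |
|---|---|---|---|---|
| 0 | 173.2 | 0% | 59.25 | 80.2% |
| 0.1 | 172.3 | 0.5% | 58.7 | 80.6% |
| 0.2 | 169.7 | 2.0% | 56.9 | 81.8% |
| 0.3 | 165.2 | 4.6% | 53.9 | 83.8% |

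At p = 0 the extra degree of freedom moves power only from 0.80252 to 0.80247. The apparent fall from 80.3% to 80.2% is rounding.

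**Step 4: how large p might be.** With r(EDSS, 6 months) = a, r(EDSS, baseline) = b and r(baseline, 6 months) = 0.5,

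p = (a − 0.5b) / √[(1 − 0.25)(1 − b²)].

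Take b = 0.3 in size as an illustration, signed so that both correlations point the same way. Then a = 0.15 gives p = 0, a = 0.20 gives 0.06, and a = 0.30 gives 0.18. A visible raw correlation between EDSS and the outcome can therefore leave little or nothing once the baseline score is in the model.

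**Step 5: chance imbalance.** Two randomised arms of 59.5 differ by up to 1.96 × √(2/59.5) = 0.36 SD in 95% of trials. An imbalance at that limit, in the part of EDSS that the baseline score does not explain, shifts the estimate by p × 173.2 × 0.36: about 6, 12 or 19 points for p = 0.1, 0.2 or 0.3, against the planned 90. This is the outer limit, not a typical imbalance.

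**The case against.** The strongest reply is that nothing here is wrong. An ANCOVA on the baseline score is valid and unbiased over randomisation, the sample size was built on exactly this model, and it reproduces. Chance imbalance is already reflected in the confidence interval and the type I error rate. All of that stands, which is why the point is optional.

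A reader might infer from the pilot that EDSS has been shown to predict the outcome. The document does not support that. Those results are before-after changes following CDT, without controls, in subgroups split at about EDSS 4.0. At most they hint at a different response to CDT, which a main-effect covariate is not meant to address. The contrast is also with patients above 4.0, whom the eligibility criteria exclude, so nothing is shown about variation within the admitted range.

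The Background statement is theoretical, is worded as a possibility, and concerns the level of self-efficacy, which the baseline score already captures. The Discussion leans the other way: it treats self-efficacy as fairly stable and does not expect even an on-study relapse to alter it much. EDSS is also obtained by phone, and measurement error would shrink any gain.

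These arguments push the likely gain down, but they do not make the addition harmful. Disease duration and gender are also absent from the stated model; that is a separate point.

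**Conclusion.** The point holds as a modest improvement. The primary model is valid and has its planned 80.3% power. Adding EDSS would raise this to between 80.6% and 83.8% if the partial correlation lies between 0.1 and 0.3, and would change nothing if it is 0. That correlation is an assumption; the document offers no figure for it. The lower end is more likely, because the EDSS range is restricted and baseline MSSES control is already in the model.

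Three stronger readings should be avoided. The text does not show that precision is lost, only that it may be. It does not show that EDSS is discarded: it is listed as baseline data, and only its absence from the stated model is established. Nor does it show that the trial is underpowered or its estimate biased.

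**What to change.** In Statistical aspects, before any outcome analysis, add one sentence that prespecifies baseline EDSS as a covariate beside condition and baseline MSSES control in the primary ANCOVA. Do the same in the similar models for the other patient outcomes. State how EDSS enters the model, for example as a single linear term, since it is an ordinal score. Keep the model without EDSS as a sensitivity analysis, so that the result stays comparable with the basis of the sample size.

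The cost is one degree of freedom and no new data. Recruitment was still under way when the article was written, so the choice could be made prospectively. Adding EDSS only after an imbalance had been seen would be open to challenge as data-driven.

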## Methods/Design

### Study design and organization

The study is a single-centre, parallel group, randomized, controlled trial to evaluate the clinical and cost effectiveness of CDT, with or without support partners, in increasing self-efficacy control in RRMS patients with low disability. The 3-day CDT is given to groups of 20 persons in Zorghotel Spelderholt, Beekbergen, The Netherlands, a facility especially equipped for the accommodation of people with impaired health. The first group was treated in April 2013. The ratio between the numbers of patients with support partner and without support partners is about 3:4. The CDTs are given from Friday to Sunday.

The control groups receive no CDT and may receive any care or treatments that are deemed necessary by the treating neurologists, MS nurses or other caregivers (‘care as usual’). In the experimental groups and the parallel control groups the baseline assessment is one week before the CDT, and in all groups the duration of follow-up is 6 months with assessments being performed at 1, 3 and 6 months.

The underlying idea of a 3-day social cognitive intervention program was conceived by the National MS Foundation The Netherlands, Rotterdam, The Netherlands (AvdZ), and further developed in collaboration with PsyToBe (RR, LD) and the other team members. The study is initiated, financed and conducted by the National MS Foundation The Netherlands, and the CDTs are organized and managed by this foundation (MvD). The contributions of the psychiatrist and the psychiatric nurse are part of regular care and are covered by the health insurance. The MS4 Research Institute is responsible for the scientific evaluations.

The study is ongoing (recruiting patients).

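### The 6-month ANCOVA uses only patients with a 6-month score; a repeated-measures model that also uses months 1 and 3 would better support the intention-to-treat statement at almost no cost

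*Protocol article*

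**What the plan says.** Statistical aspects names one time point and one model. "The primary outcome variable is the MSSES control score after 6 months", analysed by "ANCOVA with the assessment of 6 months as dependent variable and condition and baseline assessment as independent variables". It then adds: "For all other variables the 6 months values will be analysed in a similar way". The next sentence is "All analyses will be performed according to the intention-to-treat principle".

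The sample size in the same section follows this model. It takes month-6 means of 650 and 560, an SD of 200 and a baseline correlation of 0.5. It arrives at about 60 patients per condition who can be analysed, and raises the total to 140 for an expected 15% drop-out.

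Study design and organization has "assessments being performed at 1, 3 and 6 months". Aims and objectives words the primary objective as an effect "in increasing self-efficacy control (primary outcome) during 6 months after treatment". No effectiveness analysis in the article uses months 1 and 3. The article does not say that patients without a 6-month score are excluded, and it names no method for missing scores.

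**The concern.** An ANCOVA with the 6-month score as dependent variable has nothing to work with for a patient who lacks that score. Unless a further step is added, such a patient leaves the primary analysis, even when scores at months 1 and 3 are on file. For the roughly 15% the plan expects to lose, the model as described does little to support the intention-to-treat statement.

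At stake is bias in the primary estimate if drop-out differs between the arms in rate or reason after adjustment for baseline. There are reasons to guard against this. Only the CDT arm attends the course, which Ethical and privacy aspects calls demanding, and the Discussion reports 7.4% drop-out during the three days in the pilot. Controls are promised CDT once their participation ends. The outcome is self-reported by people who know whether they attended. The 6-month MSSES control score is also the effect measure in the cost-effectiveness analysis, so a bias would carry into that ratio.

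**Working it through.** **1. The plan's own figures.** Inputs from Statistical aspects: difference 650 − 560 = 90, SD 200, two-sided alpha 5%, power 80%, r = 0.5, drop-out 15%.

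- n per group = 2 × (1.960 + 0.842)² × (200/90)² ≈ 78 by the normal approximation. The exact t-test gives 78.5, so 79, as stated.
- Design factor: 1 − 0.5² = 0.75, and 79 × 0.75 = 59.25, stated as about 60.
- Drop-out: 2 × 59.25 / 0.85 = 139.4, so 140.

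All three figures reproduce.

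**2. The analysis set this implies.** 140 × 0.85 = 119 patients, or 59.5 per arm, which leaves 21 without a 6-month score. With residual SD 200 × √0.75 = 173.2, power at 59.5 per arm is 0.803 (t-test) or 0.809 (normal). Loss of power is therefore already covered, and the question is bias. Full information from all 70 per arm would give at most 0.86 to 0.87.

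**3. Bias by direct arithmetic.** Let d be the drop-out rate in an arm and g the number of points by which its drop-outs would have scored below its completers, after adjustment for baseline. Completers then overstate that arm's mean by d × g, and the bias in the difference is d₁g₁ − d₀g₀ (1 = CDT, 0 = control). The values of g, and any split of drop-out between the arms, are assumptions.

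| Drop-out CDT / control | g CDT / control | Bias (points) |
|---|---|---|
| 15% / 15% | 45 / 0 | 6.75 |
| 15% / 15% | 90 / 0 | 13.5 |
| 15% / 15% | 90 / 90 | 0 |
| 20% / 10% | 90 / 0 | 18 |
| 20% / 10% | 90 / 90 | 9 |

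**4. Simulation.** From the plan: SD 200, baseline to month-6 correlation 0.5, about 15% drop-out, true difference 90. Assumed: normally distributed scores, the remaining correlations, and how drop-out arises. Correlation set A is 0.6, 0.55 and 0.5 for baseline with months 1, 3 and 6, and 0.7, 0.65 and 0.75 for months 1–3, 1–6 and 3–6. Set B is 0.5 for baseline with every later visit, and 0.7, 0.6 and 0.7 for the same later pairs. The slope is the rise in log-odds of drop-out per SD worse score. Except in the last row, drop-out falls after month 3. In set B the last column predicts missing 6-month scores from baseline and months 1 and 3; it checks the estimate, not the standard error.

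| Drop-out mechanism | Set | ANCOVA, 6-month score present | Using months 1 and 3 |
|---|---|---|---|
| Random | B | 90.3 | 90.1 |
| Poor month-3 score, CDT only, slope 0.5 | A | 97 | about 90 |
| Same, slope 1 | A | 103 | about 90 |
| Same, slope 1.5 | B | 106.5 | 89.5 |
| Same mechanism in both arms, slope 1.5 | B | 89.8 | 89.8 |
| Slope 1 in CDT, 0.5 in control | A | 95.6 | not run |
| Opposite slopes of 1 in the two arms | A | 116 | about 90 |
| Unobserved month-6 score, CDT only | A | 110 | 101 |
| CDT only, drop-outs have no month 1 or 3 score | A | 102 | 102 |

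With no true effect, the slope 1.5 scenario in CDT only gave a spurious 17.5 points and a type I error of 9.0%.

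**5. Precision under random drop-out.** In set A, with 70 randomised per arm, the SD of the estimate was 31.5 for the ANCOVA and 30.3 with months 1 and 3. The variance ratio is (31.5/30.3)² = 1.08, so variance falls by 1 − 1/1.08 ≈ 7%. That is similar to about 119 × 0.07 ≈ 8 more analysed patients.

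**The case against.** The strongest objection is that silence is being read as a rule. A condensed article may leave the handling of missing scores to a full protocol or SAP that is not shown. That stands, and the absence of an imputation rule is not the point here. The point is that the model the article does name gives no role to scores already collected.

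Three stronger readings are tempting, and the documents do not support them.

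- **That the analysis contradicts intention-to-treat.** The principle also means analysing patients in the arm to which they were randomised, whether or not they attended the course, and this ANCOVA can do that. Sizing on patients who can be analysed and then inflating for drop-out is normal practice.
- **That the primary objective goes unanswered.** Its wording can be read as the follow-up horizon. Statistical aspects fixes month 6 and the economic evaluation uses the same score. A single end-of-follow-up endpoint is legitimate. The interim period is not wholly unused either, since costs are counted over the whole follow-up.
- **That drop-out probably differs by arm.** This is conjecture. The promise of CDT could help retain controls, and Data acquisition describes a help desk that phones participants who have trouble completing questionnaires.

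The simulated bias also depends on the scenario. Where drop-out follows the observed month-3 score, a model that uses that score is bound to recover 90. Where drop-out follows the unobserved month-6 score, 11 of 20 points of bias remain. The 116 needs opposite mechanisms in the two arms, for which the article gives no support. Finally, the repeated-measures model still omits patients with no post-baseline score. All of this limits the claim, but none of it favours leaving months 1 and 3 out.

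**Conclusion.** The point holds as a cheap improvement, not as an error that invalidates the plan. As specified, the primary model uses about 119 of 140 randomised patients at the plan's own drop-out rate and ignores the month 1 and 3 scores. A better method is available with the data already collected.

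The possible bias is about 7 to 13 points on a true 90 if drop-out follows poor month-3 scores in the CDT arm only, with slopes of 0.5 to 1 and correlation set A. It is essentially nil if drop-out is random or has the same mechanism in both arms. The article does not show which will apply. The sample size of 140 is unaffected.

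**What to change.** Make the primary analysis a likelihood-based mixed model for repeated measures on MSSES control at months 1, 3 and 6. Fixed effects are condition, visit, condition by visit, baseline and baseline by visit, with unstructured covariance. Include every randomised patient with at least one post-baseline score, in the arm assigned. Month 6 remains the primary contrast, so the endpoint does not change. A contrast averaged over months 1 to 6 is optional.

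Keep two sensitivity analyses: the 6-month ANCOVA as now written, and a delta-adjusted multiple imputation that covers all randomised patients, including those with no post-baseline score. Use the same model for secondary outcomes measured at those visits, and state in the intention-to-treat sentence how patients with missing scores enter the analysis.

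The cost is a change of wording, with no new data, visits or patients. The downside is a slightly more complex model that relies on missing-at-random and only partly corrects drop-out that depends on scores never observed. The delta-adjusted analysis is there to show how much that matters.
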